**Figure 4 fig4:**
[figure not shown]
Machine learning pipeline. Workflow diagram of the proposed Radiomics pipeline for Glioblastoma recurrence and location prediction. Preoperative MRI scans are first processed as input images, then undergo segmentation to delineate tumor volumes. Next, quantitative feature calculation extracts agnostic (texture, shape) and semantic (clinical) descriptors. The resulting high-dimensional feature set is trimmed via dimensionality reduction (feature selection and extraction), and a Classification model construction step trains a predictive algorithm. Finally, the Decision Support System: prediction of recurrence and its location integrates the model output to inform clinical follow-up and treatment planning.

Given the sample size boundaries, classical Machine Learning algorithms will serve as the primary and most clinically interpretable analytical framework for the prediction of recurrence spread. The classification capabilities of DL, specifically pre-trained convolutional neural networks (CNNs) such as AlexNet, SqueezeNet, ResNet, and GoogLeNet (Figure 5) (20), will be assessed as an exploratory secondary analysis to evaluate potential performance gains over classical ML These networks will be fine-tuned using different training strategies, including three configurations involving partial weight freezing, as well as training from scratch. Additionally, the CNNs will be used as feature extractors, whereby the learned feature representations are passed to classical ML classifiers, for example SVMs. This hybrid approach leverages the representational power of CNNs while benefiting from the simplicity and efficiency of some ML algorithms, which are particularly suitable for high-dimensional classification tasks such as those involved in this study.

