## Methods and analysis

### Study design

This retrospective study will be conducted at different Italian Units of Neurosurgery for clinical data and images acquisition, with all ML and DL analyses performed at the Department of Physics and Chemistry of the Università of Palermo (Italy) and the Department of Mathematics and Physics of the University of Salento (Italy).

The project unfolds in two successive phases spanning a total of 24 months (Figure 1). During the first 6 months, we will secure all necessary administrative approvals and ethics committee clearances, complete team training, and assemble the retrospective clinical and imaging dataset. At the same time, we will define the key instrumental parameters for prognostic feature extraction, establish standardized protocols for data handling and quality control, and design software architecture to support subsequent ML and DL workflows.

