To mitigate the inherent variability of a multicenter retrospective design, all preoperative MRIs will undergo a rigorous standardization and preprocessing pipeline prior to tumor segmentation and feature extraction. Initially, images will be subjected to N4 bias field correction to resolve magnetic field inhomogeneities. Subsequently, to ensure spatial uniformity across different scanner vendors and acquisition protocols, all scans will be co-registered to a standard anatomical space and resampled to an isotropic voxel resolution of 1x1x1 mm using appropriate interpolation techniques. Image intensity distributions will also be standardized using Z-score intensity normalization or histogram matching. Finally, to further account for residual scanner-related batch effects on the quantitative data, an advanced statistical harmonization technique, such as the ComBat method, will be applied to the extracted radiomic feature matrices prior to their integration into the machine learning classification framework.

For the development of the predictive algorithm and the automatic segmentation task, MRIs will be processed using MITK-MI brain software with the NIfTI data format. Tumor regions will be manually delineated on each slice using freehand Volume of Interest (VOI), and the software will calculate total lesion volume by summing the area of all Regions of Interest (ROIs), multiplied by slice thickness and interslice gap (Figure 3).

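### Scanner harmonisation covers the radiomic features but neither CNN route, so part of an apparent CNN gain over classical ML could be centre recognition

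*Protocol article*

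**What the plan says.** **Several centres.** Study design: "This retrospective study will be conducted at different Italian Units of Neurosurgery for clinical data and images acquisition". The number of centres is not given.

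**Image-level steps for everyone.** Radiological parameters: "all preoperative MRIs will undergo a rigorous standardization and preprocessing pipeline prior to tumor segmentation and feature extraction". These steps are N4 correction, co-registration, 1 mm resampling and an intensity step: "Image intensity distributions will also be standardized using Z-score intensity normalization or histogram matching". They apply to every scan, so the CNN inputs receive them too.

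**A further step for one model family.** The same section adds, "to further account for residual scanner-related batch effects on the quantitative data, an advanced statistical harmonization technique, such as the ComBat method", which "will be applied to the extracted radiomic feature matrices prior to their integration into the machine learning classification framework". The Analysis section describes the radiomic features as PyRadiomics shape, first-order and texture measures.

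**CNN classification.** In the Analysis section, after the Figure 4 caption, pre-trained CNNs are fine-tuned under several weight-freezing schemes or trained from scratch. In addition, "the CNNs will be used as feature extractors, whereby the learned feature representations are passed to classical ML classifiers, for example SVMs". The CNN work "will be assessed as an exploratory secondary analysis to evaluate potential performance gains over classical ML".

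**Validation.** Nested repeated stratified k-fold cross-validation, with no grouping or hold-out by centre or scanner stated.

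**The concern.** The article itself treats image preprocessing as insufficient, since it adds a step aimed at what is left. Only the radiomic models receive that step. An end-to-end CNN has no radiomic matrix to adjust, and the hybrid route sends its learned features to the classifier with no adjustment stated.

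Scanner appearance is harmless to the AUC unless it also carries information about the label. It does so if the local/distant mix differs between centres, for example through referral, surgical practice or reading. A model that identifies the centre can then rank patients from high-share centres above those from low-share centres without reading the tumour any better. Because training and test folds can contain patients from the same centres, cross-validation rewards this.

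At stake is the interpretation of the planned comparison. A positive difference for the CNNs could not be attributed to better use of tumour information, and the part due to the centre need not carry over to a new hospital.

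**Working it through.** **1. The article's own figure.** 200 screened × (1 − 0.30) = 140 analysed. This reproduces, and N = 140 is used below.

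**2. Which steps reach which model.**

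| Step | Radiomic ML | End-to-end CNN | CNN features + SVM |
|---|---|---|---|
| N4, co-registration, resampling, intensity step | yes | yes | yes |
| Harmonisation of residual scanner effects | yes | none stated | none stated |
| Folds grouped by centre | no | no | no |

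The spatial augmentation meant to help across scanning protocols is described for the 3D U-Net segmentation task, not for the CNN classifiers.

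**3. Assumptions.** The article gives neither the number of centres nor their distant shares. I assume three equal centres, 20% distant overall, and shares of 20/20/20%, 15/20/25% or 10/20/30%. Within-centre AUC is taken as 0.60 or 0.65.

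**4. AUC of a score that knows only the centre.** With weights w = 1/3, shares p_i and mean share P = 0.20:
- distribution of distant cases over centres: a_i = w·p_i / P
- distribution of local cases: b_j = w·(1 − p_j) / (1 − P)
- AUC = Σ a_i·b_j over p_i > p_j, plus ½ Σ a_i·b_i.

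At 10/20/30%: a = (0.167, 0.333, 0.500), b = (0.375, 0.333, 0.292). Ordered part = 0.333×0.375 + 0.500×(0.375 + 0.333) = 0.479. Tied part = ½ × 0.319 = 0.160. AUC = 0.64.

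At 15/20/25%: a = (0.250, 0.333, 0.417), b = (0.354, 0.333, 0.3125). AUC = 0.404 + ½ × 0.330 = 0.57.

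At 20/20/20%: AUC = 0.50.

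**5. The same score under cross-validation.** In simulated stratified 5-fold cross-validation with N = 140 and centre rates estimated in the training folds (about 112 patients), the mean AUC is 0.50, 0.54 and 0.62 for equal shares, 15/20/25% and 10/20/30%. The centre signal survives stratified folds but is weaker than the closed form suggests.

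**6. Gain when centre information is added to true within-centre discrimination.** The score is the within-centre log-likelihood ratio plus the centre log-odds, with the centre recognised perfectly.

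| Distant shares | Within-centre AUC | Gain, true rates known | Mean gain, rates learned in training folds |
|---|---|---|---|
| 15/20/25% | 0.65 | 0.01 | about 0.00 (−0.002) |
| 15/20/25% | 0.60 | 0.02 | about 0.00 |
| 10/20/30% | 0.65 | 0.05 | about 0.04 to 0.05 |
| 10/20/30% | 0.60 | 0.08 | about 0.06 |

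The last column is the relevant one, since a network has to learn the rates. Repeat runs differ slightly in the second decimal. With equal shares the centre carries no information and there is no gain.

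**7. Pairs left in a same-centre AUC.** The same-centre share of distant–local pairs is Σ a_i·b_i = 0.33 at 15/20/25% and 0.32 at 10/20/30%. With 28 distant and 112 local patients (20% of 140), that is roughly a third of 28 × 112 = 3,136 pairs.

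**The case against.** The strongest case against has five parts.

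- **A condensed article.** The CNN arm gets one short paragraph, and ComBat is offered only as an example. The harmonisation of deep features could be described in a fuller document. This has some force for the hybrid route. However, the article does not leave the scope of harmonisation open: it names the radiomic matrices. That wording cannot extend to end-to-end CNNs, which have none.
- **CNN inputs are preprocessed.** True. Only the residual effect is at issue, but the article itself says that a residual effect exists.
- **The radiomic arm is not clean either.** This stands. A reader might infer that harmonisation leaves classical ML free of centre signal. The documents do not support that. ComBat aligns each feature's location and scale by batch and need not remove every multivariate trace. The classical arm also uses clinical variables and semantic descriptors, which are not harmonised and may differ by centre.
- **The premise is undocumented and the size is bounded.** This also stands. No distant shares by centre are given. The figures assume perfect centre recognition, and the gain disappears at the milder spread. For scale, the standard error of one AUC with an assumed 28 distant cases among 140 is about 0.06.
- **Low stakes.** The CNN comparison is exploratory, and the Discussion and Conclusion defer validation and clinical utility to later prospective work. This limits the weight of the point. It does not make the planned comparison even.

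**Conclusion.** The point holds as a limited one. Followed as written, the protocol compares harmonised radiomic models with unharmonised CNN models, under a validation scheme that cannot separate tumour information from centre information. If distant shares differ between centres, part of an apparent CNN gain could be centre recognition.

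Under the assumed conditions that part averages about 0 at 15/20/25% and at most about 0.05 to 0.06 in AUC at 10/20/30%. For each assumed spread these are upper bounds, because the centre is taken to be recognised perfectly. They rest on three equal centres and 20% distant recurrence overall, neither of which the documents state. With equal shares the effect is zero.

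Two stronger readings are tempting. One is that the CNN AUC will in fact be a scanner artefact; nothing in the documents shows that scanner and outcome are associated. The other is that the main finding is compromised; classical ML is the primary framework, and this gap touches only the exploratory secondary comparison.

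**What to change.** 1. In the hybrid route, apply the same harmonisation to the CNN feature matrix before the classifier, fitted on the training folds and then applied to the held-out fold.
2. For classical ML and for both CNN routes, report beside the pooled AUC a centre-stratified AUC that compares only distant–local pairs from the same centre. For end-to-end CNNs, which have no radiomic matrix to harmonise, this is the main safeguard. It also covers centre signal that enters the classical arm through clinical and semantic variables.
3. State that no improvement of CNNs over classical ML will be claimed unless the paired difference in the centre-stratified AUC supports it.

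The cost is analysis wording and code; batch labels are already needed for ComBat. The downside is precision: with three equal centres only about a third of the pairs remain, so the interval is wider, and with about 28 distant cases (an assumption) the comparison may be inconclusive.

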**Figure 5 fig5:**
[figure not shown]
Schematic of the architecture of a convolutional neural network (CNN). A convolutional neural network (CNN) consists of a series of specialized layers that progressively transform and refine the input image into a final classification decision. First, convolutional layers apply learnable filters to extract localized features, and the ReLU (rectified linear unit) activation function is used after each convolution to introduce non-linearity and accelerate training. Pooling layers then downsample the feature maps, reducing spatial dimensions and improving invariance to small shifts. After repeating convolution + ReLU and pooling blocks to build a rich, hierarchical representation, the resulting feature maps are flattened into a single one-dimensional vector. This vector feeds into one or more fully connected layers, where each neuron computes a weighted sum of its inputs to integrate all learned features. Finally, the last fully connected layer uses a Softmax activation to convert raw scores into normalized probabilities, allowing the network to assign the input image to one of the target classes.

For the segmentation task, we will implement a 3D U-Net architecture (21), which has demonstrated excellent performance in volumetric medical image segmentation. This architecture extends the previously introduced 2D U-Net and is now widely adopted as a state-of-the-art method in the field (22, 23). Fully convolutional neural networks (CNNs) like U-Net have become the dominant strategy for automatic segmentation, particularly due to their ability to perform well even when trained on a limited number of annotated images, a common scenario in medical imaging.

The 3D U-Net architecture is composed of two main components: a contracting path and an expanding path. The contracting path captures high-resolution local features, while the expanding path reconstructs spatial resolution by upsampling global low-resolution features. By concatenating these two types of information at each stage, the network is able to integrate both local detail and broader contextual information. In our case, the 3D U-Net architecture will be specifically trained and optimized for segmenting tumor volumes using contrast-enhanced T1-weighted MRI sequences as the primary input channel. The ground truth annotations will be generated manually by two independent expert neuroradiologists, and baseline inter-rater agreement will be evaluated using the Dice Similarity Coefficient to ensure high-quality training data. To optimize the network weights, we will employ the Adam optimizer coupled with a dynamically scheduled learning rate. The training process will be guided by a hybrid loss function combining Dice Loss and Cross-Entropy Loss to effectively handle the volumetric class imbalance between the enhancing tumor regions and the background brain tissue. Furthermore, to prevent overfitting and effectively leverage the massive amount of voxel-level data contained within the 140 whole-brain 3D MRI volumes, the network will be trained utilizing extensive spatial data augmentation techniques, such as random rotations, scaling, and elastic deformations. These combined structural parameters and augmentation strategies are explicitly designed to maximize the model’s generalization capabilities across different scanning protocols.

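### The 3D U-Net's generalization across scanning protocols is credited to training settings and spatial augmentation, which are not suited to deliver it on their own

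*Protocol article*

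**What the plan says.** The 3D U-Net paragraph that closes the Analysis section gives the purpose of the augmentation as "to prevent overfitting and effectively leverage the massive amount of voxel-level data contained within the 140 whole-brain 3D MRI volumes". It then names the means: "the network will be trained utilizing extensive spatial data augmentation techniques, such as random rotations, scaling, and elastic deformations". The paragraph ends with a second, wider purpose: "These combined structural parameters and augmentation strategies are explicitly designed to maximize the model’s generalization capabilities across different scanning protocols". The other settings it names are the Adam optimizer, a scheduled learning rate and a loss combining Dice and cross-entropy. The loss is justified by the imbalance between tumour and background voxels.

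Radiological parameters describes a separate safeguard. There, "all preoperative MRIs will undergo a rigorous standardization and preprocessing pipeline prior to tumor segmentation and feature extraction". The steps are that "images will be subjected to N4 bias field correction to resolve magnetic field inhomogeneities", that "all scans will be co-registered to a standard anatomical space and resampled to an isotropic voxel resolution of 1x1x1 mm" (done "to ensure spatial uniformity across different scanner vendors and acquisition protocols"), and that intensities are standardized by Z-score or by histogram matching. ComBat follows, to deal with scanner effects that remain, but it is applied to the radiomic feature tables that go to the classifiers.

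The Analysis section also states that the U-Net does not supply features to the prediction models. It is a secondary outcome meant for later prospective use.

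**The concern.** The stated means do not match the second stated purpose. Spatial transforms show the network the same tumours in other poses, sizes and shapes. Apart from interpolation they leave voxel intensities as they were, so they do not show it a scan with a different contrast, noise level or slice thickness. The optimizer, learning-rate schedule and loss do not do so either.

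The tool is meant for multicentre use beyond the training data, so performance on an unfamiliar scanner is the property that counts. If the network is sensitive to acquisition differences, a Dice score pooled over familiar centres could look good while accuracy falls at a new one. A reader of this paragraph would believe that the risk had been designed out.

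**Working it through.** **Inputs and the plan's own figure.** Study population and sample size gives about 200 screened patients and about 30% excluded: 200 × (1 − 0.30) = 140. This matches the 140 volumes in the U-Net paragraph. The point does not depend on this number.

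**Which step meets which difference.** The list of differences is my assumption about how acquisition protocols vary; the article gives no such list.

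| Difference between scans | Preprocessing that reaches the U-Net | Named spatial augmentation | What is left |
|---|---|---|---|
| Bias field | N4 | no effect | what N4 leaves |
| Voxel grid | 1 mm isotropic resampling | not needed | nothing on the grid itself |
| Linear gain or offset | Z-score or histogram matching | no effect | nothing |
| Monotone contrast change | removed by histogram matching, only partly by Z-score | no effect | some, if Z-score is chosen |
| Acquisition noise | none | no effect | not addressed |
| Detail lost in thick slices | resampling equalizes the grid but restores no detail | scaling may help a little | largely not addressed |
| Residual scanner effects | ComBat, on radiomic features only | no effect | uncorrected at the voxel level |

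**Illustration on a synthetic 3D image.** This uses assumed data and only shows direction. The image SD within the mask is 0.177. Each change was applied, the image was standardized again, and the result was compared with the standardized unchanged image.

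- Linear change (3.2 × intensity + 40): maximum difference after Z-score about 1e-14, so it is removed.
- Contrast change (intensity to the power 1.8): mean absolute difference 0.09 SD after Z-score and 0 after histogram matching.
- Added Gaussian noise, SD 0.3: mean absolute difference 0.76 SD after Z-score and 0.49 SD after histogram matching.

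The assumed noise is large, at 0.3 / 0.177 = 1.7 times the image SD, so 0.76 and 0.49 do not forecast real scans. What carries over is that standardization can remove linear and monotone contrast differences but not noise.

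**What a centre-held-out check would cost in precision.** The article does not give the number of centres. Assume K centres of equal size and the same SD of Dice in each. A held-out centre then has 140 / K patients, training uses 140 × (1 − 1/K), and the interval for that centre's mean Dice is √K times as wide as the pooled one.

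| K (assumed) | Patients held out | Patients in training | Relative interval width |
|---|---|---|---|
| 4 | 35 | 105 | 2.0 |
| 7 | 20 | 120 | 2.6 |
| 10 | 14 | 126 | 3.2 |

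The check is therefore feasible but imprecise for any one small centre.

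**The case against.** The strongest reply is that cross-protocol robustness does not rest on augmentation alone. The preprocessing covers all preoperative MRIs before segmentation, so the U-Net benefits from it. N4 targets the bias field, resampling the voxel grid, and histogram matching, if chosen, any monotone contrast change. The training scans come from several centres and so carry real scanner variation. All of this stands.

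A reader might infer that the augmentation cannot yield cross-protocol generalization at all, or that the plan augments only what it has already standardized. The documents support neither reading. The text states a design aim for a combination of measures, not a guaranteed property. Co-registration fixes head position and grid, but not tumour size, shape or location, which the spatial transforms usefully vary. Preventing overfitting is also the first purpose given for them, and for that they are apt.

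It can also be said that the list is illustrative and that an article condenses a fuller recipe. This stands only in part. The examples are open-ended within spatial techniques, and the complaint is not about missing detail. It is about an explicit rationale that does not follow from the measures named.

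Finally, preprocessing does not settle the matter by the plan's own account. After N4, resampling and normalization, the article still expects residual scanner effects and adds ComBat for them. That correction serves the classifiers and never reaches the network's voxel input.

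**Conclusion.** The point holds with modest priority. The attribution in the U-Net paragraph is not supported as written: training settings and spatial augmentation are not suited, on their own, to produce generalization across scanning protocols. Preprocessing covers much of the gap. Acquisition noise, detail lost in thick-slice scans and, under Z-score, residual contrast differences are met by no step named for the network.

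The size of the effect on Dice is unknown and cannot be derived from the article. The conclusion assumes that the contributing scanners differ in noise, slice thickness or non-linear contrast. That is plausible for a multicentre retrospective series, but the article does not quantify it. The primary prediction models are unaffected, because their features come from manual segmentations.

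**What to change.** 1. Keep the spatial augmentation and give overfitting as its purpose. Add random contrast and brightness changes, noise, blur and simulated thick-slice downsampling to the U-Net training.
2. Report Dice with each centre held out in turn, beside the pooled Dice. Group small centres where needed, and give intervals.
3. Reword the closing sentence of the U-Net paragraph so that robustness across protocols is credited to the harmonization under Radiological parameters and to the added augmentation, and so that any claim goes no further than the held-out result.

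The cost is a small change to the training pipeline and one further training run per held-out centre or group. No new patients or readers are needed. The downsides are compute time and wide intervals for small centres. If the extra runs are not feasible, step 3 without reference to the added augmentation or a held-out result is the minimum: credit the harmonization and drop the claim that the augmentation secures generalization across protocols.
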